# SAMPLE SIZE:

Using the formula for sample size calculation (Chow S, Shao J, Wang H. 2008).

$$n=\frac{r+1}{r}\frac{{{SD}^{2}\left( Z_{\beta}+Z_{\alpha/2} \right)}^{2}}{d^{2}}$$

Where:

SD **=** standard deviation from a previously published study=2

d=expected mean difference between the groups

r=ratio for the groups= 1:1

$Z_{\beta}$**=**standard normal variation for level of power=80% power is 0.84

Z$\alpha/2$= standard normal variation for level of significance= 1.96

In a similar study done by Katheria AC(24), using the mean value for haemoglobin for UCM and DCC, we get our sample size as follows:

$$n=\frac{1+1}{1}\frac{{2^{2}\left( 0.84+1.96 \right)}^{2}}{{0.7}^{2}}$$

n= 128 per arm

To account for attrition bias an additional 10 percent will be added to the total sample size.

Therefore a total sample size of 280 will be required for the study.

# Study procedures

### PATIENT RECRUITMENT

Potential study participants will be recruited by the attending midwife at the triage area in labour ward as well as though the antenatal wards on a daily basis. The subjects are identified and chosen for the study if they meet the eligible criteria (inclusion and exclusion). Women will be enrolled at onset of spontaneous labour (cut off point <7 cm cervical dilation) if they are in labour or when the decision has been made for caesarean delivery for those not in labour. Recruitment and enrolment will be carried out by the research assistants, attending midwife or principal investigator who are all part of the study team.

### Consent

Once identified, the principal investigator or research assistant will brief the patients on the purpose and method of the study and verbal consent will be attained. Thereafter Consent will be given in written form, on a pre designed consent form. The consent form provided will describe the purpose of the study, the study procedure to be followed as well as the potential benefits and risks of participating in the study. Any pertinent questions regarding the study from the parent/guardian will be answered at this point.

This process will be free from coercion and will be explicitly voluntary.

Those who accept to take part in the study will be asked to sign the consent form which will be counter signed by the investigator. Records will be kept regarding reasons for non participation of eligible participants. The investigator or research assistant will then countersign the consent form. A copy of the signed consent form will be given to the participant.

A log will be available in Labour ward of the principle investigators, research assistants and enrolled patients. Data will be then collected from the eligible patients and every entry signed in the log book.

All consenting patients who meet the eligible criteria will be monitored as labour progresses until delivery when they will be immediately randomized into the two different intervention groups.

### Randomization

Randomization will be done by the midwives carrying out the interventions who are part of the study in labour ward. Randomization will be done when delivery is imminent. This is characterised by urge to bear down or second stage of labour. For caesarean delivery randomization will be done at induction of anaesthesia in the operating theatre.

The statistician will use block randomization in equal blocks of 14 until the total sample size is achieved. They will be randomized into two groups. A random allocation sequence will be done on computer generated slips of paper bearing the allocation code which will be kept in serially numbered opaque sealed envelopes with an unpredictable allocation code. Recruited patients will be randomly assigned to either the control arm or the intervention arm in a 1:1 ratio.

Using STATA statistical package randomization ado package, computer generated random sequences in blocks of 4 and 6 will be used to determine the order of intervention allocation and avoid anticipation of the allocation group for the next patient while maintain a balance of the patients recruited in each of the arms at each point. The randomly generated list of the allocation sequence will be printed on small cards each representing the allocation of each patient in the order generated by the software. Each of these cards will be sealed in opaque envelopes that will be sequentially numbered in the order of the list generated.

After identifying an eligible patient and consent granted the next sequentially numbered envelope will be opened and then will determine which arm the patient will be allocated. Each participant will be assigned a unique 4 digit number for subject identity and confidentiality.

### Blinding

The nature of the intervention makes it impossible to blind the clinicians performing the intervention. Although study staff will not inform the mothers of their allocation, the nature of the intervention makes it impossible to blind them. If an already randomized mother later becomes ineligible, the assigned allocation code will not be re-used. The principle investigator or the research assistants will monitor the delivery and therefore will not be blinded to treatment assignment.

The laboratory staff performing analysis of blood samples will be blinded to the allocation group.

### Intervention groups:

A structured survey questionnaire will be used to gather obstetrical and medical details from mothers that meet study criteria during the first stage of labour. The questionnaire will be filled in by the research assistants or principal investigator. Once delivery is imminent, the midwife will immediately open a sealed, numbered, opaque envelope containing the treatment allocation. Neonates will undergo either umbilical cord milking or delayed cord clamping.

For neonates undergoing UCM, after delivery the cord will be pinched as close to the placenta as possible and milked towards the infant over 2 second duration. The cord is then released and allowed to refill over 1 to 2 seconds between each milking motion. This is repeated a total of 4 times. After milking the cord will be clamped and handed over to the neonatal receiving team.

For neonates undergoing DCC, the cord will be clamped after waiting 60 seconds. Timing will be noted by using a stop watch timer in the labour ward delivery room and a wall mounted clock in the maternity theatre.

The position of the new born during DCC or UCM will be on the maternal abdomen for both caesarean delivery as well as after spontaneous vaginal delivery.

Early care of the new born should be initiated, including drying and stimulating for first breath or cry. Maintain normal temperature with skin to skin contact and covering the infant with dry linen. Secretions should be cleared if only copious or appear to be obstructing the airway.

DCC and UCM should not interfere with active management of third stage of labour including Uterotonics agents after delivery of the newborn to minimize bleeding.

If placental circulation is not intact, such as in the case of placental abruption, abnormal placentation, and cord avulsion as well as Newborns without spontaneous breathing during the first 10 seconds of life, with major congenital malformations diagnosed at birth and with tight nuchal cord will be subjected to early cord clamping based on need for resuscitation, regardless of the assigned intervention.

Clinicians and midwives involved in the delivery will be trained on the process of UCM by live clinical tutorials and videos.

All patients irrespective of which group they are in will be reviewed by consultants and senior house officers during the ward rounds.

### DATA COLLECTION.

### Maternal data

Obstetric and medical information will be collected from maternal health care records from the time of admission to antenatal care these included reported illness, medication, parity, blood group Rhesus factor status, and Haemoglobin values. This data will be collected by the research assistants or principal investigator. After giving birth, the estimated maternal postpartum blood loss will be recorded by the midwife within two hours after delivery. During postnatal care, mothers will be interviewed within 24 hours of delivery in the post natal ward to further to complete the questionnaire.

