# Study objectives

Research question:

Is there a difference in haemoglobin, haematocrit and neonatal jaundice between preterm infants who will undergo umbilical cord milking versus delayed cord clamping?

Broad objective:

To determine the effects of umbilical cord milking versus delayed cord clamping on haemoglobin, haematocrit, and neonatal jaundice of preterm neonates.

Primary objectives:

Among preterm neonates at 28-36 weeks who will undergo umbilical cord milking versus delayed cord clamping at vaginal or caesarean delivery, to:

1. Determine and compare the mean haemoglobin and haematocrit values at 24 hours of life.

Null hypothesis: There is no difference in the mean haemoglobin and haematocrit values 24 hours after birth comparing pre term neonates delivered at 28-36 weeks who will undergo umbilical cord milking versus delayed cord clamping.

1. Determine and compare the incidence rate of neonatal polycythemia at 24 hours of life.

Null hypothesis: There is no difference in the incidence rate of neonatal polycythemia at 24 hours after birth comparing pre term neonates delivered at 28-36 weeks who will undergo umbilical cord milking versus delayed cord clamping.

1. Determine and compare the incidence rate of neonatal jaundice within the first week of life.

Null hypothesis: There is no difference in the incidence rate of neonatal jaundice within the first week of life comparing pre term neonates delivered at 28-36 weeks who will undergo umbilical cord milking versus delayed cord clamping.

Secondary objectives:

Among preterm neonates at 28-36 weeks who will undergo umbilical cord milking versus delayed cord clamping at vaginal or caesarean delivery, to:

1. Determine and compare the incidence rate of neonatal anaemia within the first 24 hours of life.
2. Determine and compare the incidence rate of maternal primary post partum haemorrhage within 24 hours of delivery.

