# RESEARCH METHODOLOGY

### STUDY DESIGN

Single blind, open-label, Randomised controlled trial.

This will be a parallel group study with 1:1 randomisation. Application of block randomization will be used with 140 participants in each arm comparing neonatal venous haemoglobin and haematocrit values between umbilical cord milking and delayed cord clamping among preterm babies delivered at Kenyatta National Hospital, Nairobi 24 hours after birth.

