#### Clinical jaundice

With assistance from the paediatrician who will be part of the study team, clinical examination of the neonate will be carried out observing for yellow discolouration in the periphery of the ocular conjunctiva and in the oral mucous membranes (under the tongue, hard palate). Information will be filled on the data collection form by the research assistant. Mothers will be trained before discharge on how to detect jaundice and contact information will be given to them. Mothers will be trained by the paediatrician on how to detect jaundice by way of pictures and videos on how to detect jaundice(38).Telephone calls will be made to participants on day three as well as day seven postpartum regarding neonatal follow-up for those discharged earlier. Contact information of principal investigator will be given to the mothers if they wish to contact the principal investigator at any time in-between the follow up calls.

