### DATA VARIABLES

- Primary dependent variables; the infants’ venous haemoglobin and haematocrit value will be measured at 24 hours of life. Polycythemia, Neonatal jaundice and need for phototherapy/exchange transfusion
- Secondary dependent variables: neonatal anaemia, maternal primary post partum haemorrhage.
- Independent variables: Delayed cord clamping (control) and Umbilical cord milking (intervention).

#

[figure not shown]

Excluded (n= )

- Multiple gestation (n= )
- Declined consent (n= )
- Major congenital abnormalities (n= )
- Red cell isoimmunisation(n= )
- Positive serology HIV/Hep/VDRL (n= )
- Tight nuchal cord (n= )
- Ante partum haemorrhage (n= )
- Need for neonatal resuscitation (n= )

Assessed for eligibility (n= )

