**BASELINE QUESTIONNAIRE**

**Part I: Socio demographics**

**Indicate all times using the 24 hour clock, and dates in this format date/month/year.**

DATE__________

Code number of mother-infant pair:_________ Randomization arm: ___

Date of Signed Informed Consent: ____/______/_____

Copy given to patient: Yes / No

1. Age of mother (years) ……………………………….
2. Marital Status

Single □ Widowed □

Married □ Separated □

Divorced □

1. Level of Education

Primary □ Secondary □ Tertiary □

1. Employment status

Self employed □ Salaried employment □ Unemployed □

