**Part V: Follow up**

MATERNAL COMPLICATIONS

Post partum haemorrhage yes □ No □

Post partum anaemia Yes □ No □

Post partum sepsis Yes □ No □

NEONATE COMPLICATIONS

Clinical Jaundice Yes □ No □

Polycythemia Yes □ No □

Neonatal sepsis Yes □ No □

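### Jaundice is exposed to ascertainment bias, PPH is measured over 2 hours but defined over 24, and phototherapy/exchange transfusion has no field on the data form

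*Protocol*

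**What the plan says.** **Blinding.** Study Design describes the trial as "Single blind, open-label, Randomised controlled trial". The Blinding section states that clinicians cannot be blinded, that the principal investigator or research assistants watch the delivery and are not blinded, and of the mothers that "the nature of the intervention makes it impossible to blind them". Only laboratory staff are blinded.

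**Jaundice.** Study Objectives and Data Variables list it as primary; the Abstract lists it as secondary. Under Clinical Jaundice it is a visual examination made with a paediatrician's help, and a research assistant completes the form. For infants who go home early, "Mothers will be trained before discharge on how to detect jaundice and contact information will be given to them", and calls follow on days 3 and 7. Appendix III opens with a "Randomization arm" entry, and its Part V offers one tick-box, "Clinical Jaundice Yes" or No.

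**PPH.** The secondary objective is: "Determine and compare the incidence rate of maternal primary post partum haemorrhage within 24 hours of delivery". Operational Definitions set thresholds of 500 ml for vaginal and 1000 ml for caesarean delivery over 24 hours. Under Maternal Data, "the estimated maternal postpartum blood loss will be recorded by the midwife within two hours after delivery". Randomization and Intervention Groups have midwives open the envelope and carry out the intervention.

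**Phototherapy.** Data Variables includes "need for phototherapy/exchange transfusion" among the primary dependent variables, and dummy Table 3 has a row for phototherapy.

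**The concern.** Laboratory blinding protects haemoglobin and haematocrit. It does nothing for outcomes that depend on someone looking, estimating or reporting while aware of the arm. Jaundice and PPH are both of that kind.

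Two further problems lie in collection rather than blinding. The PPH measurement window is shorter than the outcome window, and the form lacks items that the protocol's own definitions and dummy tables need. At stake are the credibility of the jaundice comparison, the number of PPH events captured and the ability to check them against the definition, and whether phototherapy and exchange transfusion are systematically recorded at all.

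**Working it through.** **The protocol's own figure.** The only calculated design figure is for mean haemoglobin: n = 2 × 2² × (0.84 + 1.96)² / 0.7² = 2 × 4 × 7.84 / 0.49 = 128 per arm. Adding 10% to 256 gives 281.6, against 280 stated. It reproduces but does not bear on this point. The protocol gives no expected rate for jaundice, PPH or phototherapy.

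**What is needed against what the form holds (Appendix III, Parts I–V).**

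| Item | Where the protocol needs it | Field on the form |
|---|---|---|
| Blood loss in ml, to 24 h | Operational Definitions; secondary objective | None; PPH Yes/No only |
| Index mode of delivery | PPH threshold; dummy Table 1; CONSORT figure | None; the only such column covers past pregnancies (Part II) |
| Phototherapy/exchange transfusion | Data Variables; phototherapy also in dummy Table 3 | None |
| Clamp time | Neonatal Data (stopwatch or wall clock) | None |
| Serum bilirubin | Dummy Table 4 | None; the only blood test described is a complete blood count |
| Date and source of the jaundice result | First-week objective; examination or call | None; Yes/No only |

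The screening form (Appendix II) names both delivery routes without recording which occurred. The contents list Appendix V as a log of follow-up calls, but the appendix itself is an identity log with no column for a result.

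**Jaundice: effect of unequal detection.** All rates here are assumptions. Take no true difference, 140 per arm, and detection of 0.95 in one arm and 0.85 in the other. The expected risk ratio is 0.95 / 0.85 = 1.12. With recorded rates p1 and p2, difference d and mean p̄:

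- SE0 = √(2p̄(1−p̄)/140); SE1 = √((p1(1−p1) + p2(1−p2))/140)
- False-positive rate = Φ((d − 1.96·SE0)/SE1) + Φ((−d − 1.96·SE0)/SE1)
- True rate 20%: recorded 19% v 17%, d = 0.02, SE0 = SE1 = 0.0459 to four places; Φ(−1.53) + Φ(−2.40) ≈ 0.072.
- True rate 60%: recorded 57% v 51%, d = 0.06, SE0 = 0.0596, SE1 = 0.0595; Φ(−0.95) + Φ(−2.97) ≈ 0.171.

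Equal detection (0.90 in both arms) returns 5.0%. A wider gap, 0.95 v 0.75, gives a risk ratio of 1.27 and 14% to 52% over the same true rates.

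**PPH: effect of a 2-hour cut-off that acts equally in both arms.** Assume true rates of 20% v 10%, 140 per arm, and power = Φ((d − 1.96·SE0)/SE1).

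| Share of cases captured | Recorded rates | Risk ratio | Power |
|---|---|---|---|
| 100% | 20% v 10% | 2.0 | 65% |
| 80% | 16% v 8% | 2.0 | 54% |
| 60% | 12% v 6% | 2.0 | 42% |

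For 10% v 5%, power falls from 35% to 29% and 23%. The ratio does not move; events and power are lost. If detection did differ by arm (0.95 v 0.85) with equal true PPH rates of 5–15%, the false-positive rate would be only 5.5–6.6%.

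**The case against.** The best defence is that the protocol has second routes. Mothers are interviewed within 24 hours to complete the questionnaire, and Part V has a PPH box, so some later bleeding may be caught. PPH and need for phototherapy are named as expected adverse events, which the principal investigator reviews daily and which go to the ethics committee within 24 hours. A paediatrician helps with the jaundice examination, and nothing says that the paediatrician knows the arm. The Blinding section is candid about who is unblinded. The sample size rests on haemoglobin, and phototherapy is called primary only under Data Variables.

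Much of this stands, and it limits the conclusion. A reader might infer that the clinical outcomes will be biased or cannot be analysed. The documents do not support that. Jaundice and PPH each have a field, bias requires detection or reporting to differ by arm, and nothing shows that it will or in which direction. A reader might also suppose that the arm affects time to discharge, and so how jaundice is ascertained; the protocol gives no evidence of this. Nor does it say that whoever watched a delivery always enters that infant's result.

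The second routes do not close the gaps. Neither the interview nor adverse-event reporting has a stated blood-loss volume, and adverse-event reporting is not a systematic record of phototherapy for every infant. This is also not a matter for a statistical analysis plan, which cannot recover data that were never recorded.

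**Conclusion.** The point holds as a risk and a collection gap, and should be corrected.

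- **Jaundice** is at risk of ascertainment bias of unknown size and direction. The 7–17% false-positive range illustrates a 10-point detection gap; it rests wholly on assumed rates and is not a prediction.
- **PPH** after 2 hours is liable to be missed. That means lost events and power, not necessarily a biased risk ratio. The form data cannot verify the mode-specific definition.
- **Phototherapy/exchange transfusion** has no field, although it is listed as primary in one section. Clamp time and bilirubin have none either.
- **The blinding label** contradicts itself and does not match the Blinding section.

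Haemoglobin and haematocrit, on which the sample size rests, are not affected.

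**What to change.** 1. Complete cumulative blood loss (ml) to 24 hours at or after the postnatal interview already planned. Otherwise, restate the outcome as blood loss by 2 hours.
2. Add fields to Appendix III for blood loss, index mode of delivery, clamp time, phototherapy/exchange transfusion, and the date and source (examination or call) of the jaundice result. Either collect bilirubin or drop it from dummy Table 4.
3. Move the "Randomization arm" entry to the separate allocation log. Where the roster allows, have the jaundice examination and the day-3 and day-7 calls done by staff who were not at that delivery. Removing the entry alone does little if the person completing the form attended the birth.
4. Replace "Single blind, open-label, Randomised controlled trial" with open-label with blinded laboratory assessment. Do not claim blinded outcome assessment for mother-reported jaundice or midwife-estimated PPH, because those informants still know the arm.

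The cost is a form revision, some extra data entry and a roster constraint, which could be felt with two research assistants. Collecting bilirubin would add a test; dropping it from the table costs nothing. The sample size does not change.

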#### Neonatal data

The research assistants will measure the time from complete delivery of the baby to the first clamp on the umbilical cord with a stopwatch or using the wall clock. The infant will be taken care of as per normal protocol after delivery once allocated intervention has been carried out. Blood samples for a full blood count will be obtained 24 hours after delivery in the neonatal ward by the phlebotomist. Data will be collected by the research assistants and filled in on the data collection form.

#### Blood samples

All neonatal blood samples will be collected using a 23-gauge needle from a peripheral vein, amounting 0.5mls by the attending paediatric resident as per the hospital protocol. Blood will be collected in EDTA tubes (BD Vacutainer®).The blood sample will be transported in a blood transport box by the research assistant to the Kenyatta national hospital laboratory and analysed for ‘complete blood count’: Hb, Hct, MCV, mean cell haemoglobin concentration (MCHC). Complete blood counts will be analysed using the automated haematology analyser. The results will be collected by the research assistant and the data filled into the data collection form by the research assistant.

#### Clinical jaundice

With assistance from the paediatrician who will be part of the study team, clinical examination of the neonate will be carried out observing for yellow discolouration in the periphery of the ocular conjunctiva and in the oral mucous membranes (under the tongue, hard palate). Information will be filled on the data collection form by the research assistant. Mothers will be trained before discharge on how to detect jaundice and contact information will be given to them. Mothers will be trained by the paediatrician on how to detect jaundice by way of pictures and videos on how to detect jaundice(38).Telephone calls will be made to participants on day three as well as day seven postpartum regarding neonatal follow-up for those discharged earlier. Contact information of principal investigator will be given to the mothers if they wish to contact the principal investigator at any time in-between the follow up calls.

